**Methods:**

We will conduct a stepped wedge cluster randomized controlled trial in eight public hospitals with each having least 3000 deliveries a year. Each hospital will represent a cluster with an intervention transition period of 2 months in each. With a level of significance of 95%, the statistical power of 90% and an intra-cluster correlation of 0.00015, a study period of 19 months should detect at least a 15% change in intrapartum-related mortality. Quality improvement training, mentoring, systematic feedback, and a continuous improvement cycle will be instituted based on bottleneck analyses in each hospital. All concerned health workers will be trained on standard basic neonatal resuscitation and essential newborn care. Portable fetal heart monitors (Moyo®) and neonatal heart rate monitors (Neobeat®) will be introduced in the hospitals to identify fetal distress during labor and to improve neonatal resuscitation. Independent research teams will collect data in each hospital on intervention inputs, processes, and outcomes by reviewing records and carrying out observations and interviews. The dose-response effect will be evaluated through process evaluations.

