### Settings

Each hospital manages at least 3000 deliveries a year (Table 1). Their intrapartum-related mortality rates range from 11 to 36.5 intrapartum-related deaths (intrapartum stillbirth and first-day mortality) per 1000 births. All the hospitals have separate labor units and operating theaters. Normal and complicated vaginal deliveries take place in the labor units and cesarean sections in the operating theaters. Each hospital has a postnatal unit and a sick newborn care unit. The hospitals provide level II sick newborn care services [32].

**Table 1 Tab1:** Total birth and mortality rate in the study hospitals (2017)

	Total no. births	Intrapartum stillbirth rate (per 1000 births)	First-day neonatal mortality rate (per 1000 live births)	Intrapartum-related death rate (per 1000 births)
Koshi Zonal Hospital	5464	9.3	4.4	13.7
Janakpur Regional Hospital	14,300	11.9	23	34.9
Bharatpur Hospital	11,006	7.3	3.7	11.0
Lumbini Zonal Hospital	8649	11.2	12.3	23.5
Dadeldhura Sub-Regional Hospital	3112	10.3	4.4	14.7
Mid-Western Regional Hospital	3847	5.0	25	30.0
Bheri Zonal Hospital	4132	1.2	35.3	36.5
Seti Zonal Hospital	6277	2.2	29.7	27.9

Intrapartu-related mortality is the composite of intrapartum stillbirths and first-day mortality data

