### Sample size

The intervention will be employed in the same hospital. Therefore, every hospital will be included in control as well as intervention groups. This fact will produce the correlated data between the arms. For binary correlated data, we have considered the one-sided McNemar’s test for sample size calculation. Considering the statistical power of 90%, level of significance at 5% and the average cluster size of 4800 deliveries we have calculated the sample size. For adjusting the cluster effect, the sample size is adjusted by the design effect. The design effect is chosen as a proxy of 1.71 based on Nepal’s Demographic Health Survey 2016 [37]. This design effect is updated based on our average cluster size. The design effect for NMR in NDHS 2016 is reported as 1.12 for urban sample with an average cluster size of 799. Based on the information, we have calculated the intra-cluster correlation coefficient (ICC) of 0.00015 which gives the design effect 1.71 for average cluster size 4800 [38]. We have also considered the 7% loss to follow up to reach the final sample size of 31,259 deliveries in each group. This number will be proportionally allocated among the hospitals. The STATA command “power” is used for necessary calculation.

Purposive sampling will be used in the qualitative components of the study. Maximum variation sampling will guide the selection of participants to in-depth interviews with health workers and focus group discussions with the hospital management team. This approach secures a wide variety of people of interest and consequently a broad range of perspectives to better understand contextual factors influencing on implementation. A convenient sample of pregnant women will be interviewed about their experiences of intrapartum care. Sample sizes will be based on data saturation (Table 2).

**Table 2 Tab2:** Number of health workers in the study hospitals (2017)

	Nurses	Doctors	Other health workers	Total health workers
Koshi Zonal Hospital	25	8	45	78
Janakpur Regional Hospital	60	22	0	82
Bharatpur Hospital	86	20	17	123
Lumbini Zonal Hospital	81	7	36	124
Dadeldhura Sub-Regional Hospital	42	2	13	57
Mid-Western Regional Hospital	20	3	22	45
Bheri Zonal Hospital	33	4	26	63
Seti Zonal Hospital	32	6	56	94

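### The planning ICC of 0.00015 does not fit the hospitals in Table 1, and under a stepped-wedge variance the stated 90% power is not reached, mostly for reasons other than the ICC

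*Protocol article*

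**What the plan says.** The Sample size section starts from a survey figure: "The design effect for NMR in NDHS 2016 is reported as 1.12 for urban sample with an average cluster size of 799". From this it derives its planning values: "we have calculated the intra-cluster correlation coefficient (ICC) of 0.00015 which gives the design effect 1.71 for average cluster size 4800". The design effect multiplies a sample size from a paired test ("we have considered the one-sided McNemar’s test for sample size calculation"), with these settings: "Considering the statistical power of 90%, level of significance at 5% and the average cluster size of 4800 deliveries". The result is given as follows: "We have also considered the 7% loss to follow up to reach the final sample size of 31,259 deliveries in each group".

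The abstract repeats "an intra-cluster correlation of 0.00015" together with 90% power and the claim that "a study period of 19 months should detect at least a 15% change in intrapartum-related mortality".

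The Settings section reports 2017 data for the eight hospitals that are the clusters: "Their intrapartum-related mortality rates range from 11 to 36.5 intrapartum-related deaths" per 1000 births. Table 1 gives each hospital's births (3,112 to 14,300) and rates. The article does not compare these rates with the planning ICC.

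**The concern.** The survey ICC concerns a different outcome (neonatal mortality, not intrapartum stillbirth plus death in the first 24 hours) and a different kind of cluster. Better-matched data are in the same article, and a threefold spread in hospital rates is hard to square with an ICC of 0.00015. The design effect 1 + (m − 1) × ICC belongs to a parallel cluster trial. In a stepped wedge, precision depends on within-hospital contrasts adjusted for calendar time, and on how stable each hospital's rate is.

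At stake is the headline claim of 90% power on a mortality outcome. If true power is much lower, a null result could be misread as evidence from a well-powered trial that the package does not work.

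**Working it through.** **1. The plan's own figures.** ICC = (1.12 − 1)/(799 − 1) = 0.12/798 = 0.00015. Design effect = 1 + 4799 × 0.00015 = 1.72, against 1.71 stated. Working back, 31,259 × 0.93/1.71 = 17,000 per group before inflation. Neither the baseline rate nor the within-pair correlation behind 17,000 is stated. At Table 1's birth-weighted 24.4 per 1000 and a 15% relative reduction, a one-sided McNemar calculation comes close with a within-pair correlation of about 0.40: 16,965 × 1.71/0.93 = 31,194. With independent groups the answer would be about 51,900.

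**2. What 0.00015 implies.** SD = √(0.00015 × 0.0244 × 0.9756) = 1.9 per 1000, so about 95% of hospitals should lie within 24.4 ± 1.96 × 1.89, or 20.7 to 28.1. Six of the eight printed rates lie outside (11.0, 13.7, 14.7, 30.0, 34.9, 36.5). The observed SD is 9.9 per 1000. Sampling noise does not close the gap: the mean binomial sampling variance is 4.19 × 10⁻⁶ (SD 2.0 per 1000), and √(1.9² + 2.0²) = 2.8.

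**3. ICC from Table 1.**
- One-way ANOVA with unequal sizes: between-hospital mean square 0.7544, within 0.02371, n₀ = 6,826. ICC = (0.7544 − 0.0237)/(0.7544 + 6,825 × 0.02371) = 0.0045.
- Moments: (9.83 × 10⁻⁵ − 0.42 × 10⁻⁵)/(0.0240 × 0.9760) = 0.0040.
- With Seti at 31.9 instead of the printed 27.9: 0.0046 and 0.0042.
- A rough 95% range (chi-square, 7 df, on the moment estimate) is 0.0017 to 0.017. Its lower end is about 11 times 0.00015.

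**4. Power under a stepped-wedge variance.** Figure 2 is not available, so the layout is assumed: 19 monthly periods, one hospital crossing every 2 months, transition months dropped, fixed month effects, and rate 24.4 per 1000. The 15% is read as relative, so the difference is 0.15 × 0.0244 = 0.00366. A hospital-month mean has variance ICC·v + v(1 − ICC)/m and covariance ICC·v·CAC with other months, where v = p(1 − p) and CAC is the cluster autocorrelation. The SE comes from generalised least squares, averaged over random hospital orders. Power = Φ(0.00366/SE − z), with z = 1.645 one-sided or 1.960 two-sided.

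All births at Table 1 volumes (56,787 × 17/12, about 80,400 retained):

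| ICC | CAC | SE | One-sided | Two-sided |
|---|---|---|---|---|
| 0.00015 | 1 | 0.00190 | 61% | 49% |
| 0.001 | 1 | 0.00212 | 53% | 41% |
| 0.004 | 1 | 0.00218 | 51% | 39% |
| 0.017 | 1 | 0.00218 | 51% | 39% |
| 0.004 | 0.95 | 0.00231 | 48% | 35% |
| 0.004 | 0.80 | 0.00266 | 39% | 28% |

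With only 2 × 31,259 = 62,518 deliveries, at ICC 0.00015 and then 0.004 (CAC 1):
- Spread over the 17 retained months, the SE rises from 0.00212 to 0.00246 and one-sided power falls from 53% to 44%.
- Spread over all 19 months, the SE rises from 0.00222 to 0.00260 and one-sided power falls from 50% to 41%.

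**5. Attribution.** Of the 39-point gap between 90% and 51%, 29 points (90% to 61%) arise with 0.00015 left in place. Correcting the ICC accounts for the other 10.

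**The case against.** The survey ICC is openly offered as a proxy and the arithmetic on it is correct, so this is a poorly sourced assumption and not a calculation error. That stands.

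A reader might put 0.0040 to 0.0046 into the plan's own formula, obtain a design effect of 20 to 23 (1 + 4799 × 0.0040 = 20.2), and conclude that the trial is too small by more than a factor of ten. The documents do not support that. Each hospital serves as its own control, stable differences between hospitals largely cancel, and the parallel formula does not apply. The Sample size section recognises the pairing, however crudely, by choosing a paired test.

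Table 1 also has limits. It covers one year and eight hospitals, with crude rates for all births, whereas the trial enrols consenting women beyond 22 weeks with a fetal heart sound at admission. The balance of the two components differs sharply (Bheri 1.2 and 35.3, Bharatpur 7.3 and 3.7), so recording differences may contribute. This makes 0.004 imprecise and argues for a range. It does not rescue 0.00015.

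Above about 0.001 the ICC hardly matters if hospital rates are stable. Autocorrelation matters more, but no document gives a value for it.

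The cluster size of 4800 could also be reasonable. Half of 19 months less a 2-month transition is 8.5 months, and 7,098 × 8.5/12 = 5,028 births per hospital per condition; 8 months gives 4,732. That reading is an inference; the article does not state the basis.

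**Conclusion.** The concern holds in a limited form and should be fixed. The planning ICC conflicts with the article's own hospital data, by a factor of about 27 to 31 on the point estimates and about 11 at the lower end of the rough range. That ratio is not the loss of precision. Under the assumed layout, moving from 0.00015 to 0.004 raises the SE by about 14% (0.00190 to 0.00218) and costs about 10 points of power. The cost is larger if hospital rates drift: one-sided power is about 39% at an assumed autocorrelation of 0.8.

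The larger problem is the method. A paired test with a parallel design effect stands in for a stepped-wedge variance with time effects, and no scenario examined comes near 90%. It would be wrong to infer that the ICC alone undermines the power.

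The power figures depend on the assumed layout, the 24.4 per 1000 baseline and the relative reading of 15%. The mismatch between the ICC and Table 1 does not depend on the layout or on the size of the effect.

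**What to change.** - Recompute power, or the detectable effect at 90%, with a stepped-wedge variance formula that includes time effects, the actual step layout and actual hospital volumes.
- Use an ICC range informed by Table 1, for example 0.001 to 0.017, and cluster autocorrelation from 0.8 to 1.0. Report the result for the planned one-sided test, with the two-sided figure beside it.
- State the basis of the 4800 cluster size and the baseline rate used.
- Reconcile the Seti row of Table 1: 2.2 + 29.7 = 31.9, printed as 27.9, which is below its first-day component alone. The conclusion does not depend on which is right.
- Restate the power or detectable effect in both the abstract and the Sample size section.

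The hospital rates and volumes are already printed and the sponsor has the step layout, so no new data are needed. The cost is a less favourable stated power.

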## Methods

### Trial design

The trial is a stepped wedge cluster randomized controlled trial in eight public hospitals in Nepal. Each hospital will represent a cluster randomized in a cross-sectional wedge design with intervention transition period in each hospital in 2 months (Fig. 2). With the qualitative research components, we aim to provide insight into women’s and staffs’ response to intervention and to understand how contextual factor affect its implementation [31].

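### The stated 90% power for a 15% change rests on a paired McNemar calculation in a design without pairs, and 31,259 deliveries per group does not follow from the article's own figures.

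*Protocol article*

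**What the plan says.** The Trial design section describes different women measured before and after crossover: "Each hospital will represent a cluster randomized in a cross-sectional wedge design". The Sample size section notes that every hospital serves in both conditions and concludes: "This fact will produce the correlated data between the arms". On that ground the authors write that "we have considered the one-sided McNemar’s test for sample size calculation". The other inputs are given as "Considering the statistical power of 90%, level of significance at 5% and the average cluster size of 4800 deliveries", then an ICC of 0.00015 and a design effect of 1.71. The calculation ends: "We have also considered the 7% loss to follow up to reach the final sample size of 31,259 deliveries in each group". The abstract turns this into the claim that "a study period of 19 months should detect at least a 15% change in intrapartum-related mortality", with 90% power.

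The Sample size section states no baseline rate, no discordant proportion and no within-pair correlation, and does not mention calendar time. The only baseline figures are in the Settings section: "Their intrapartum-related mortality rates range from 11 to 36.5 intrapartum-related deaths" per 1000 births, with hospital values in Table 1.

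**The concern.** McNemar's test compares two outcomes on the same subject or on a matched pair. Its gain in efficiency comes from the correlation within pairs. Here no woman is seen under both conditions and no matching of deliveries is described. Sharing a hospital produces intra-cluster correlation. That is a different quantity, and the same paragraph already handles it through the design effect. If the sample size takes credit for pairing that does not exist, 31,259 is too small for the stated 90%.

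A stepped wedge must also separate the intervention from calendar time, because intervention months fall later than control months. That costs precision, and the calculation has no term for it. If the real power for 15% is well below 90%, a null result on mortality could be misread as evidence that the package does not work.

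**Working it through.** **Inputs.** From the Sample size section: 31,259 per group, 7% loss, design effect 1.71, ICC 0.00015, one-sided 5%, power 90%. From the abstract: 15% change, read as a relative reduction, and 19 months. From Table 1: 56,787 births a year and a births-weighted intrapartum-related death rate of 24.4 per 1000. Using that rate is an assumption. With it, p1 = 0.02440, p2 = 0.85 × p1 = 0.02074 and d = 0.00366.

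**1. Undo the inflation.** 31,259 × 0.93 = 29,071, and 29,071 / 1.71 = 17,000. The base sample size was evidently 17,000 per group.

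**2. Try to reproduce 17,000 with McNemar.** With D the discordant proportion, n = [1.645 × √D + 1.282 × √(D − d²)]² / d².

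| Within-pair correlation | D | n | n × 1.71 / 0.93 |
|---|---|---|---|
| 0 | 0.0441 | 28,213 | 51,875 |
| 0.00015 (the stated ICC) | 0.0441 | 28,208 | 51,867 |
| 0.40 | 0.0265 | 16,965 | 31,194 |

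The printed figure is matched at a correlation of about 0.40.

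**3. Could another baseline explain it?** At zero correlation, the highest hospital rate in Table 1 (36.5 per 1000) still needs 18,641. Reaching 17,000 takes about 39.9 per 1000, above every hospital. The Seti row of Table 1 does not add up (2.2 + 29.7 = 31.9, printed 27.9), but correcting it moves the mean only to 24.8 per 1000 and the required correlation to 0.39.

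**4. Power without pairing, keeping the 1.71.** Power = Φ(d / SE − z), with SE = √{[p1(1 − p1) + p2(1 − p2)] / n}, where the bracket is 0.0441.
- After 7% loss, n = 17,000: SE = 0.001611 and d / SE = 2.272. One-sided Φ(2.272 − 1.645) = 73%; two-sided Φ(2.272 − 1.960) = 62%.
- All 31,259 analysed, n = 31,259 / 1.71 = 18,280: 76% one-sided, 65% two-sided.

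**5. Power with calendar time adjusted.** This is a generalised least squares variance with a random hospital effect and a category for each month, for 8 hospitals over 19 months. The assumed layout has one hospital crossing every 2 months and its 2 transition months excluded. All births then means 56,787 / 12 × 17 = about 80,400. The planned number after loss is 2 × 29,071 = 58,142. Besides 0.00015, an ICC of 0.004 was used as an assumption: the standard deviation of the Table 1 rates is 0.0099, and 0.0099² / (0.0244 × 0.9756) is about 0.004.

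| Deliveries analysed | ICC | One-sided | Two-sided |
|---|---|---|---|
| All births (about 80,400) | 0.00015 | about 64% | about 51% |
| All births (about 80,400) | 0.004 | about 54% | about 41% |
| Planned number after loss (58,142) | 0.00015 to 0.004 | about 54% to 43% | about 41% to 32% |

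**6. Power with no time adjustment and no 1.71.** The formula of step 4 with n = 29,071 gives 91% one-sided, and with n = 31,259 gives 92%.

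**The case against.** The strongest reply is that 1.71 is an inflation for parallel clusters. In a stepped wedge each hospital is its own control, so that penalty does not carry over directly. Step 6 shows that a before-after comparison without it reaches 91% to 92% one-sided, close to the claim. A reader might infer from step 4 that 73% is the most this trial can achieve; step 6 shows that it is not a ceiling. But the route to 90% assumes no secular trend, which a stepped wedge should not rely on and which the article does not state. It also drops an inflation that the article says it applied.

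A reader might also infer from step 5 that the trial's true power is known to be around half the stated 90%. The documents do not support that. The Fig. 2 schedule is not visible here, the ICC of 0.004 is read off the spread in Table 1, and the article leaves the analysis strategy for later. Part of the fall from 73% to the two-sided figures is sidedness, not time adjustment; the like-for-like comparison is the one-sided column.

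The baseline rate is likewise inferred. Table 1 covers all births in 2017, while the trial enrols consenting women with a fetal heart sound at admission. The 0.40 is therefore back-calculated, and the authors' own input is unknown. None of this supplies pairs, or reconciles 0.40 with 0.00015.

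**Conclusion.** The sample-size justification is wrong as written. That McNemar does not fit a cross-sectional design is certain. That 31,259 cannot be obtained from the stated inputs without a pairing correlation near 0.40 holds for a 15% relative reduction at the Table 1 mean, and no hospital rate in that table removes the need for pairing.

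The size of the power shortfall is less certain. On the article's own design effect it is 73% to 76% one-sided instead of 90%. With calendar time adjusted, it is about 43% to 64% one-sided (32% to 51% two-sided) across the two ICCs and the two numbers analysed, conditional on the assumed layout. The 51,900 per group measures the inconsistency and is not a recruitment target: two such groups make 103,800 deliveries, more than the roughly 80,400 non-transition births that Table 1 volumes yield in 19 months.

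**What to change.** Delete the McNemar calculation. Recompute with a cross-sectional stepped-wedge method that includes hospital and period effects, the actual Fig. 2 schedule, Table 1 hospital sizes, exclusion of the transition months, and a justified ICC with a sensitivity range. State the baseline rate, the effect size as absolute or relative, and the sidedness of the test. Then restate, in both the abstract and the Sample size section, either the power for a 15% reduction or the reduction detectable at 90%. The figure printed should come from that calculation and not from the assumed layout used here.

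Enrolment need not change. The cost is one recalculation, the rewording of two sections and a less favourable stated power.

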### Randomization

Using a simple random technique, the principal investigator will generate a random sequence among the eight hospitals to determine the temporal stepped wedge sequence of the clusters through simple random technique. The allocation of the introduction of intervention in each hospital will be done in a stepped wedge pattern based on the above randomly generated sequence. Blinding is part of the SW-RCT—clusters/hospitals will not know when the other hospitals will be controls or intervention.

### Data collection

An independent team will be established in each hospital to collect data on implementation, process, and outcomes.

*Implementation level data—*a form will be used to collect data on the number of stakeholders engaged in each intervention:A hospital readiness and service availability assessment tool will be used to conduct the bottleneck analysis of service readiness for intrapartum care. A planning tool will be used to develop a plan based on the bottleneck analysis.Data on health workers’ knowledge and skills on intrapartum care before and after training will be collected using multiple-choice questions and skills checklist.The data on the continuous quality improvement process will be collected using a Plan-Do-Study-Act diary, which was tested in our previous study [21].The periodic performance of the health workers will be done using a skills checklist.

*Process level data—*A separate system will be established to collect data on health worker performance in simulated and clinical intrapartum care settings:Data will be collected on the use of the NeoNatalie Live® manikin through skill drills in an application-based system.The use of fetal heart rate monitor (Neobeat®) will be assessed by a separate group of data collector using an observation checklistData on health worker performance on monitoring fetal heart rates, immediate newborn care, and neonatal resuscitation will be collected using an observation checklist.The implementation of the SUSTAIN interventions using the PARIHS framework [39] will be evaluated through in-depth interviews and focus group discussions with service providers and caregivers.The acceptability of the new interventions will be assessed by studying health worker acceptance and barriers to use.The perceptions of women about intrapartum care will be evaluated with semi-structured interviews.

*Outcome level data—*data on mortality and clinical events during intrapartum care will be collected from patient case notes and labor and delivery registers.

*Socio-demographic data—*the socio-demographic characteristics of the women will be collected through semi-structured interviews.

*Equipment data*—signal data and events that are automatically recorded by the Safer Births equipment will be uploaded to a cloud service with strict access control. Equipment data will be analyzed to complement the process level data and drive local QI processes, they will be analyzed to check the integrity and condition of the equipment and the data will be used to create new insight, develop improved equipment as well new signal analysis methods.

